### Primary outcomes

1. Traditional smoking cessation: percentage of subjects that were current (in TC and Mixed groups) or former (in EC group) smokers reporting sustained smoking abstinence from traditional cigarette smoking at 6, 12, 24, 36 and 60 months. Smoking abstinence is defined as complete abstinence from tobacco smoking (not even a puff) for the 30 days period prior to the visit.

2. Decrease in the number of traditional cigarettes smoked: average difference in self-reported number of traditional cigarettes smoked per day at baseline and 6, 12, 24, 36 and 60 months in the groups TC and Mixed.

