### Secondary outcomes

1. Adherence to e-cigarette smoking: number of months of continued e-cigarette smoking in groups EC and Mixed.

2. Traditional and electronic smoking (overall smoking) cessation: percentage of subjects in all groups reporting sustained smoking abstinence from both traditional and electronic cigarette smoking at 6, 12, 24, 36 and 60 months. Smoking abstinence is defined as complete abstinence from tobacco or electronic smoking (not even a puff) for the 30 days period prior to the visit.

3. Time to hospital admission for one of the followings: cardiovascular diseases, chronic obstructive pulmonary diseases, cancer of the lung, esophagus, larynx, oral cavity, bladder, pancreas, kidney, stomach, cervix, and myeloid leukemia. Repeated admissions of the same subject will be counted once and the subject will be censored at the date of the first admission.

4. Rate of subjects with smoking-related hospitalizations: percentage at 1, 2, 3 and 5 years of subjects who had a hospital admission for one of the followings: cardiovascular diseases, chronic obstructive pulmonary diseases, cancer of the lung, esophagus, larynx, oral cavity, bladder, pancreas, kidney, stomach, cervix, and myeloid leukemia. Repeated admissions of the same subject will be counted once.

5. Number of smoking-related hospitalizations: mean number at 1, 2, 3 and 5 years of hospital admissions for one of the followings: cardiovascular diseases, chronic obstructive pulmonary diseases, cancer of the lung, esophagus, larynx, oral cavity, bladder, pancreas, kidney, stomach, cervix, and myeloid leukemia. Each admissions of the same subject will be counted.

6. Number of hospitalizations for cardiovascular diseases: mean number at 3 and 5 years of hospital admissions for cardiovascular diseases. Each admissions of the same subject will be counted.

7. Number of hospitalizations for smoking-related cancers: mean number at 3 and 5 years of hospital admissions for cancer of the lung, esophagus, larynx, oral cavity, bladder, pancreas, kidney, stomach, cervix, and myeloid leukemia. Each admissions of the same subject will be counted.

8. Self-reported quality of life: average quality of life according to EuroQoL EQ-5DL at 6, 12, 24 and 36 months. The analysis of quality of life will follow the technical specifications recommended by the EuroQol group [29].

9. Reported side effects at 6, 12, 24, 36 and 60 months.

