### Sample size estimation

The primary analyses will compare: (A) the primary outcome 1 (rate of traditional smoking sustained cessation) across the groups TC, Mixed and EC (only the subjects that were former traditional smokers); (B) the difference in the number of traditional cigarettes smoked per day between baseline and end of follow-up in groups TC and Mixed.

As regards primary analysis 1, conservatively assuming a 5-year cessation rate of 20% in the TC group, and 30% in the Mixed group (EC group most probably having a higher cessation rate), we would need 313 subjects per group to achieve a power of 80%. Given the need of multivariate modeling and an expected 20% rate of withdrawals/dropouts, 500 subjects would be required in each group.

Concerning primary analysis 2, assuming a 5-year reduction in the number of smoked traditional cigarettes of 2 ± 6 and 4 ± 6 in the Mixed group, with the same above parameters (alpha error = 0.05; beta-error = 0.20; dropout/withdrawals = 20%), we would only require 240 subjects per group.

We will thus conservatively enroll a minimum of 500 subjects in each group (EC, TC and Mixed), for a total of 1500 participants.

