### Data analysis

All data will be collected and initially handled by the Coordinating unit, which is responsible for privacy regulations and maintains the property.

At each time-point, the differences in the rates of traditional smoking cessation (or other categorical outcomes such as adverse events) across groups will be first examined using Fisher’s exact test. Cox proportional hazards analysis will be used to calculate the adjusted relative hazards of traditional smoking cessation (and smoking-related hospitalization) by each variable. Stochastic level of entry into the model will be set at 0.10, with age, gender, and smoking groups forced to entry, and multicollinearity, interactions with time to event and higher-power terms will be explored for all variables in the final model. A minimum events-to-variable ratio of 10 will be maintained in multivariate modeling to avoid overfitting, and Schoenfeld’s test will be performed to check the validity of proportional hazards assumption. Kaplan-Meier survival analysis will also be used to examine the association between hospitalization and smoking group. The validity of constant incidence ratios over the follow-up will be checked using Nelson-Aalen cumulative hazard estimates.

Multiple linear regression will be used to investigate the predictors of the difference in the number of traditional cigarettes smoked between baseline and each time-point of follow-up. Additional multivariate models such as mixed-effect logistic models will be explored for both the primary and secondary outcomes to account for repeated observations and the potential distortions of the variability in the exposure to traditional cigarette smoking by the participants in groups EC and Mixed (for which also stratification will be considered) [31]. In all mixed models, the cluster variables will be participant’s id, nicotine level of the electronic and traditional cigarette and exposure to past traditional cigarette smoking. We will assume and independent correlation structure for all clusters, but we will also repeat all models setting an exchangeable correlation structure.

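### Primary outcome 1 is called sustained abstinence but defined as 30-day point prevalence, and the Cox model for cessation, on its ordinary reading, estimates a third quantity

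*Protocol article*

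**What the plan says.** All references are to the protocol article.

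- *Primary outcomes*, item 1, reports the percentage of "smokers reporting sustained smoking abstinence from traditional cigarette smoking at 6, 12, 24, 36 and 60 months". The next sentence gives the only operative rule: "Smoking abstinence is defined as complete abstinence from tobacco smoking (not even a puff) for the 30 days period prior to the visit". *Secondary outcomes*, item 2 (overall smoking), repeats both the label and the 30-day rule.
- *Sample size estimation* names the outcome of primary analysis A as the "rate of traditional smoking sustained cessation", compared across TC, Mixed and the former smokers in EC. It assumes 20% (TC) and 30% (Mixed) at 5 years and gives 313 per group for 80% power.
- *Data analysis* first examines "At each time-point, the differences in the rates of traditional smoking cessation" by Fisher's exact test. It then states: "Cox proportional hazards analysis will be used to calculate the adjusted relative hazards of traditional smoking cessation". No event, event date or relapse rule is given for that model.
- A first-event rule is written for hospital admission only (*Secondary outcomes*, item 3): "Repeated admissions of the same subject will be counted once and the subject will be censored at the date of the first admission".
- On repeated status the plan says: "Additional multivariate models such as mixed-effect logistic models will be explored for both the primary and secondary outcomes to account for repeated observations".
- *Interventions and groups* defines EC participants as not smoking traditional cigarettes at entry.

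**The concern.** The label and the rule describe different outcomes. Nothing requires abstinence at an earlier visit or since a quit date. At month 60 the rule covers about one of the preceding 24 months. A person who quit five weeks before the visit counts as sustained, and so does one who smoked for most of the interval. The CO check is made at the follow-up contact, so it does not turn the 30-day rule into a sustained one.

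The adjusted analysis adds a second mismatch. Fisher's test uses status at a visit, so a person smoking again at month 60 is a failure there. An ordinary single-event Cox model takes the first abstinent visit as the event and does not use what follows. For EC former smokers the event precedes entry, so a hazard of cessation during follow-up has no meaning, although they belong to primary comparison A.

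At stake is what the primary result means. A rate reported as sustained cessation would be a 30-day rate, and the unadjusted and adjusted results could differ because they answer different questions.

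**Working it through.** **1. The plan's own figure.** Inputs from *Sample size estimation*: 20% v 30%, alpha 0.05 (taken as two-sided), power 80%.

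- Uncorrected: n = [1.96·√(2·0.25·0.75) + 0.8416·√(0.2·0.8 + 0.3·0.7)]² / 0.10² = (1.2002 + 0.5119)² / 0.01 = 293.2, so 294.
- With continuity correction: (293.2/4)·[1 + √(1 + 4/(293.2·0.10))]² = 312.8, so 313.

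This matches exactly. The study was therefore sized on two proportions at 5 years, not on Cox events. After 20% dropout, 500 per group leaves 400. Uncorrected power is then Φ[(0.10·√400 − 1.2002)/0.6083] = Φ(1.315) = 90.6%.

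**2. How far the quantities separate.** The documents give no relapse rate, so this is illustration. Assume a two-state monthly model starting from smoking, with quit probability q and relapse probability r per month, one month standing for 30 days. Put λ = 1 − q − r.

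- Abstinent at month t: A(t) = q/(q+r)·(1 − λ^t). For each r, q is set so that A(60) = 20%.
- Ever abstinent at a visit: 1 − the product of [1 − A(g)] over the gaps g = 6, 6, 12, 12, 24.
- Abstinent at both 36 and 60 months: A(36)·S, with S = [q + r·λ^24]/(q+r).

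| r per month | q | Ever abstinent at a visit | Abstinent at both 36 and 60 |
|---|---|---|---|
| 0 | 0.00371 | 1 − (1−q)^60 = 20.0% | 0.125·1 = 12.5% |
| 1% | 0.00504 | 1 − 0.9709²·0.9443²·0.8979 = 24.5% | 0.1408·0.7973 = 11.2% |
| 4% | 0.01059 | 1 − 0.944²·0.903²·0.851 = 38.2% | 0.177·0.437 = 7.7% |

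All three rows have the same 30-day rate at month 60. The gap between 20% and the ever-abstinent column comes wholly from relapse. The gap to the last column exists even at zero relapse (12.5%), because people who quit between months 36 and 60 cannot meet a two-visit rule.

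**3. Direction of the comparison.** Take five equal intervals, a quit probability of 0.10 per interval in both groups, and relapse of 0.4 v 0.2.

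- Ever abstinent: 1 − 0.9⁵ = 41.0% in both groups, so a first-event model sees no difference.
- Abstinent at the end: (0.1/0.5)(1 − 0.5⁵) = 19.4% v (0.1/0.3)(1 − 0.7⁵) = 27.7%.

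**4. Power under a stricter definition.** Suppose 20% and 30% are 30-day rates and only a share s of each is sustained. Power at 400 per group, by the formula in step 1, is 90.6% at s = 1, 80.9% at 0.8, 66.2% at 0.6, 57.1% at 0.5 and 47.0% at 0.4. The two-visit column in step 2 corresponds to s of about 0.63, 0.56 and 0.39 for the 20% group.

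**The case against.** The strongest reply is that this is a condensed article. Event date, relapse rule and tie handling are commonly left to an analysis plan, which is not shown and could define the event as quitting without relapse. That stands against several stronger readings.

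- A reader might infer that the Cox model is specified to treat cessation as permanent, so that relapsers count as successes. The text does not say so; it is the ordinary reading of a model whose event is undefined.
- A reader might infer that Cox is the primary result. It is the only adjusted method named for cessation, but primary analysis A is stated as a comparison of rates, rates are examined first by Fisher's test, and 313 is a two-proportion figure.
- A reader might infer that the reported rates would be grossly inflated. That depends on the definition of sustained. With 1% quit and 4% relapse per month, 60-month prevalence is 0.2·(1 − 0.95^60) = 19.1%, and 17.6% are abstinent at every visit from their first abstinent one, which is 92% of those counted. However, 0.947²·0.908²·(1 − 0.858) = 10.5 of those 17.6 points are people first seen abstinent at month 60, about whom the rule establishes only 30 days.
- Ties at five visits are a minor matter, since standard software handles them.

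The mixed-effect logistic models would use status at every visit and so register relapse. They are only to be explored, so they mitigate the problem without resolving it. It is also fair that two analyses with different targets do not in themselves contradict each other.

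The label is untouched by these replies. An unseen plan cannot make a 30-day rule sustained without changing the stated primary outcome. Nor can it give EC former smokers an onset of cessation during follow-up.

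**Conclusion.** The label is wrong as written. Followed literally, the plan reports 30-day point prevalence under the name of sustained cessation, in the primary outcome, in secondary outcome 2 and in the sample-size statement. This rests on the text alone.

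The Cox point holds in a smaller form. On the ordinary first-event reading, the adjusted model estimates time to first abstinent visit. That differs from the 60-month proportion that sized the study and is undefined for EC former smokers. How much it matters depends on relapse. The two quantities coincide at zero relapse, differ by 4 to 5 points at 1% per month, and by about 18 points at 4%. These figures assume constant monthly rates and a 60-month 30-day rate of 20%. They show a range and are not a forecast.

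**What to change.** Choose one of two routes for primary outcome 1, and align secondary outcome 2 and the sample-size text with it.

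- **Define sustained abstinence across visits:** 30-day abstinent with CO check at the index visit and at the preceding visit, with no smoking reported between them. Keep the 30-day figure as a secondary point-prevalence outcome. Baseline smokers cannot meet this rule before month 12, so the 60-month comparison should carry the conclusion.
- **Rename:** call the outcome 30-day point-prevalence abstinence and drop the word sustained.

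Under either route:

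- Use the same definition at 60 months for the unadjusted test and the adjusted analysis, for example logistic regression at 60 months.
- If a Cox model is kept, label it time to first abstinence, make it secondary, limit it to TC and Mixed, and state its event, event date and handling of relapse.
- State to which definition the 20% and 30% refer.

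Renaming costs wording only. The across-visit route may need one question on any smoking since the last contact. The questionnaire is not shown and may already ask this, and it is to be tested on 50 participants in any case. The drawback is that reported rates may be lower. If 20%/30% were 30-day rates, power falls as in step 4 of the working, and the sample size would need to be revisited.

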### Secondary outcomes

1. Adherence to e-cigarette smoking: number of months of continued e-cigarette smoking in groups EC and Mixed.

2. Traditional and electronic smoking (overall smoking) cessation: percentage of subjects in all groups reporting sustained smoking abstinence from both traditional and electronic cigarette smoking at 6, 12, 24, 36 and 60 months. Smoking abstinence is defined as complete abstinence from tobacco or electronic smoking (not even a puff) for the 30 days period prior to the visit.

3. Time to hospital admission for one of the followings: cardiovascular diseases, chronic obstructive pulmonary diseases, cancer of the lung, esophagus, larynx, oral cavity, bladder, pancreas, kidney, stomach, cervix, and myeloid leukemia. Repeated admissions of the same subject will be counted once and the subject will be censored at the date of the first admission.

4. Rate of subjects with smoking-related hospitalizations: percentage at 1, 2, 3 and 5 years of subjects who had a hospital admission for one of the followings: cardiovascular diseases, chronic obstructive pulmonary diseases, cancer of the lung, esophagus, larynx, oral cavity, bladder, pancreas, kidney, stomach, cervix, and myeloid leukemia. Repeated admissions of the same subject will be counted once.

5. Number of smoking-related hospitalizations: mean number at 1, 2, 3 and 5 years of hospital admissions for one of the followings: cardiovascular diseases, chronic obstructive pulmonary diseases, cancer of the lung, esophagus, larynx, oral cavity, bladder, pancreas, kidney, stomach, cervix, and myeloid leukemia. Each admissions of the same subject will be counted.

6. Number of hospitalizations for cardiovascular diseases: mean number at 3 and 5 years of hospital admissions for cardiovascular diseases. Each admissions of the same subject will be counted.

7. Number of hospitalizations for smoking-related cancers: mean number at 3 and 5 years of hospital admissions for cancer of the lung, esophagus, larynx, oral cavity, bladder, pancreas, kidney, stomach, cervix, and myeloid leukemia. Each admissions of the same subject will be counted.

8. Self-reported quality of life: average quality of life according to EuroQoL EQ-5DL at 6, 12, 24 and 36 months. The analysis of quality of life will follow the technical specifications recommended by the EuroQol group [29].

9. Reported side effects at 6, 12, 24, 36 and 60 months.

All outcomes will be self-reported; primary outcome 1 and secondary outcome 2 will be checked using portable CO analyzers, and secondary outcomes 3–7 will be checked using hospital discharge abstracts through a linkage to fiscal codes (for the residents in Abruzzo only). The permission will be granted from each participants and hospitalization data will be provided by the Regional Healthcare Agency of Abruzzo. The admissions for each of the conditions included in the composite outcomes will be defined as follows, based upon the ICD-9-CM principal diagnosis codes in the Italian hospital discharge abstracts (SDO):

– COPD or asthma - 490, 490.0, 491.1, 491.2, 491.21, 491.8, 491.9, 492.0, 492.8, 494, 494.0, 494.1, 496, 493.00, 493.01, 493.02, 493.10, 493.11, 493.12, 493.20, 493.21, 493.22, 493.81, 493.82, 493.90, 493.91, 493.92 [30]

– Myocardial infarction - 410.0-410.9

– Congestive heart failure - 428.0-428.9

– Transitory cerebrovascular ischemia - 435.0-435.9

– Stroke - 433.0-434.9

– Cancer of the lung - 162.0-162.9

– Cancer of the esophagus - 150.0-150.9

– Cancer of the larynx - 161.0-161.9

– Cancer of the oral cavity - 140.0-149.9

– Cancer of the bladder - 188.0-188.9

– Cancer of the pancreas - 157.0-157.9

– Cancer of the kidney - 189.0

– Cancer of the, stomach - 151.0-151.9

– Cancer of the cervix - 180.0-180.9

– Myeloid leukemia - 205.0-205.9

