The enrolment period will last from June to December 2013. Each subject will be requested to compile a structured questionnaire at the time of enrolment at after 6, 12, 24, 36 and 60 months (and eventually, in the case of an expansion of the follow-up, at 84 and 120 months). After the first contact, the follow-up questionnaires will be compiled through a phone interview or through a specifically created website (http://www.ipazienti/fumo), with private password. To reduce potential misclassification, the level of carbon monoxide in expired after breath will be evaluated in all subjects declaring no traditional cigarette smoking in any phase of the follow-up, using portable carbon monoxide analyzers (Smokerlyzer ® piCO + ™, Bedfont Scientific Ltd.). Such an assessment will be made by the investigators, after specific periodical calibration, directly at the home of the participant or at the office of his/her general practitioner. Among the methods to monitor self-reported smoking cessation, also the assessment of cotinine in saliva can be made using portable and relatively economical devices, and such test showed a slightly higher sensitivity/specificity than tests based upon exhaled CO [27]. However, we were not able to find a seller of cotinine portable tests on saliva, and the measurement of breath CO still showed high levels of sensitivity (>90% [27,28]).

Each participant will have to sign a written informed consent. The study protocol has been registered in Clinicaltrials.gov (NCT01785537) and approved by the Ethics Committee of the University of Chieti (Record n. 6; 25-03-2013).

Participants will be enrolled at various study sites within the Abruzzo and Lazio Region using the same standardized procedures.

All the subjects that will be excluded because of past episodes of selected smoking-related major diseases will be requested to participate into a nested case–control pilot study, in which we will collect hospital admission data retrospectively and compare the rates of smoking-related diseases according to the present and past smoking habits.

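### As printed, a declared zero that the CO test contradicts is checked for cessation but still counts as a full reduction in primary outcome 2

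*Protocol article*

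**What the plan says.** Under Primary outcomes, item 1 is cessation of traditional smoking: "Smoking abstinence is defined as complete abstinence from tobacco smoking (not even a puff) for the 30 days period prior to the visit". Item 2 is the "average difference in self-reported number of traditional cigarettes smoked per day at baseline and 6, 12, 24, 36 and 60 months", in TC and Mixed.

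The text closing the Secondary outcomes section says how each outcome is verified: "All outcomes will be self-reported; primary outcome 1 and secondary outcome 2 will be checked using portable CO analyzers". Secondary outcomes 3 to 7 are checked against hospital discharge abstracts. Primary outcome 2 appears on neither list.

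Under Study design and population, the CO measurement has a general purpose and a broad target: "To reduce potential misclassification, the level of carbon monoxide in expired after breath will be evaluated in all subjects declaring no traditional cigarette smoking", at any phase of follow-up. Follow-up questionnaires are completed by phone or website. The investigators measure CO separately, at the participant's home or the general practitioner's office.

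Under Sample size estimation, primary analysis B compares "the difference in the number of traditional cigarettes smoked per day between baseline and end of follow-up in groups TC and Mixed". Under Data analysis, "Multiple linear regression will be used to investigate the predictors of the difference in the number of traditional cigarettes smoked". Neither section mentions a CO-based correction of the count.

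**The concern.** In TC and Mixed, declaring no traditional smoking does two things at once: it claims cessation for primary outcome 1 and supplies a zero for primary outcome 2. The plan collects an objective check on that declaration and names the first outcome as its use, but not the second.

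A false zero is the largest overstatement of reduction that a participant can produce, because the whole baseline count is credited as reduction. A small share of such values can therefore move a group mean noticeably. If contradicted zeros are more frequent in Mixed than in TC, or come from heavier smokers, the excess appears as an apparent advantage of dual use in a primary comparison. The two primary outcomes could also tell different stories about the same participants, although the information needed to align them is already being collected.

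**Working it through.** **1. The texts side by side.**

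| Element | Primary outcome 1 | Primary outcome 2 |
|---|---|---|
| Source | Self-report | Self-report |
| CO-checked according to the outcome list | Yes | Not listed |
| CO result planned for a declared zero | Yes | Yes, from the same test |
| Printed rule after a failed test | None | None |

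The third row follows from the testing rule, since CO "will be evaluated in all subjects declaring no traditional cigarette smoking in any phase of the follow-up". An analyst who follows the printed definition of primary outcome 2 enters the self-reported zero.

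**2. The planned effect.** Sample size estimation gives: "assuming a 5-year reduction in the number of smoked traditional cigarettes of 2 ± 6 and 4 ± 6 in the Mixed group". Reading the first value as TC, the planned difference is 4 − 2 = 2 cigarettes per day, with SD 6. The article's 240 per group does not reproduce from its stated beta of 0.20. 2 × 6² × (1.96 + 0.842)² / 2² = 141.3, so 142, and 142 / 0.8 = 178. At 90% power the figures are 190 and 190 / 0.8 = 238. That mismatch is a separate, conservative matter, and nothing below depends on it.

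**3. Error formula.** Let f be the share of a group whose declared zero is false and is contradicted by CO, and m their true cigarettes per day at follow-up. The group's mean reduction is overstated by f × m. The contrast Mixed minus TC shifts by

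f(Mixed) × m(Mixed) − f(TC) × m(TC).

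With a common m this is (excess share) × m, or 0.01 × m per percentage point. With equal shares and equal m it is zero, although both group means remain inflated.

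**4. Plausible m.** The article gives no baseline counts, but its assumptions bound them. If 30% of Mixed quit and the mean reduction is 4, quitters' mean baseline is at most 4 / 0.30 = 13.3 per day. For TC it is at most 2 / 0.20 = 10 per day. Both bounds assume that non-quitters do not increase on average. If false-zero participants resemble quitters and have not truly reduced, m is about 10 to 13.

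**5. Illustrative excess.** The article gives no rate of contradicted claims, so 2 to 5 points is an assumption. The lower end needs no difference in honesty. Apply 20% and 30% as the shares declaring zero, and assume that one claim in five is contradicted in each group. Then 0.20 × 20% = 4% in TC and 0.20 × 30% = 6% in Mixed, a 2-point excess. A 5-point excess would need claims to be less reliable in Mixed as well.

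**6. Result.**

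| Excess | m | Shift per day | Share of planned 2 |
|---|---|---|---|
| 2 points | 10 | 0.02 × 10 = 0.20 | 10% |
| 2 points | 13.3 | 0.02 × 13.3 = 0.27 | 13% |
| 5 points | 10 | 0.05 × 10 = 0.50 | 25% |
| 5 points | 13.3 | 0.05 × 13.3 = 0.67 | 33% |

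**7. Effect on the test.** With 500 × 0.8 = 400 per group and SD 6, the standard error of the contrast is 6 × √(2/400) = 0.424. With no true difference and a shift b, the two-sided 5% test rejects with probability 1 − Φ(1.96 − b/0.424) + Φ(−1.96 − b/0.424). This is about 8% for b = 0.20, 22% for b = 0.50 and 35% for b = 0.67.

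**The case against.** The strongest reply is that nothing printed instructs anyone to keep a value known to be false. The purpose of CO testing is stated generally, and the outcome list may simply name the abstinence outcomes because CO cannot yield a daily count. A condensed article may also leave failed-test handling to fuller documents. This limits the point but does not remove it. The article does not merely omit a detail: it fixes primary outcome 2 as self-reported and allocates the check outcome by outcome without it.

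Three further objections stand.

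- A reader might infer that the same person is formally a smoker in one primary outcome and a maximal reducer in the other. The documents do not support that as stated fact. No failed-test rule is printed for primary outcome 1 either, so reclassification there is inferred from the words about checking and misclassification.
- A reader might also take a positive test as proof that the zero was false. The article reports sensitivity above 90% but gives no specificity or cut-off. The test takes place apart from the phone or web declaration, so smoking may have occurred in between. The test counts against the zero but does not supply the true number.
- Replacing every contradicted zero by the baseline count can over-correct. Someone who fell from 20 to 3 per day would be scored 0 instead of 17.

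A larger bias, up to half of the planned difference, would need a 5-point excess at 20 per day (0.05 × 20 = 1.0). That baseline sits poorly with the article's own assumptions, which imply at most about 13 per day for quitters in Mixed.

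**Conclusion.** The point holds in limited form. As printed, a CO-contradicted zero stays in primary outcome 2 as a full reduction, although the check has been made and is used for cessation. That the same result would overturn the cessation claim is an inference.

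The size is not derivable from the article. The range of about 0.2 to 0.67 cigarettes per day, 10% to 33% of the planned difference, rests on an assumed excess of 2 to 5 points in Mixed, on false-zero participants resembling quitters with no true reduction, and on non-quitters not increasing on average. No figure in the article shows that contradicted zeros will differ between groups. If they do not differ in share or true consumption, the contrast is unaffected and only the group means are inflated. The change is worth making because it uses a result already planned for collection and protects a primary outcome.

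**What to change.** Amend item 2 of Primary outcomes and the verification text that closes Secondary outcomes as follows:

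- The CO check also applies to declared zeros in primary outcome 2.
- When CO contradicts a zero, the investigator re-asks and records the daily number at the test contact, and that number is used.
- If no number is given, the zero is not used and the value is treated as missing.
- Sensitivity analyses use, in turn, the last non-zero report, the baseline count (zero reduction) and the unmodified self-report.

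State the consequence of a failed test for primary outcome 1 in the same place, so that the two outcomes can be read together.

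The cost is a short addition to the text and one question at a contact that already takes place, with no new measurement. The mean reduction may come out smaller than under pure self-report. False non-zero reports, which are never CO-tested, remain uncorrected.
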